##### Edinburgh’s postpartum depression scale (EPDS)

This questionnaire is used to measure postnatal depression as well as depression during pregnancy, first developed by Cox et al. in 1987. This instrument consists of 10 multiple-choice questions (with four options). In some items, the choices are ordered from low to high (items 1, 2, and 4), while in other cases from high to low (items 3, 5, 6, 7, 8, 9, 10). The options for each item claim a score from 0 to 3 based on the severity of symptoms. The score gained by the person is obtained through summing up the scores of the ten items, which can vary from 0 to 30. This questionnaire will be completed through an interview by the researcher when the mother refers to routine checkups during 32–36 weeks of gestation. The mothers acquiring scores above the threshold limit of 12 have depression with different severity. Also, 6 weeks into postpartum, we will complete the questionnaire again via an interview to examine postnatal depression. The validity of this scale using the method of determining the concurrent correlation coefficient was calculated to be 0.78. Also, the reliability using Cronbach alpha method and split-half method was estimated as 0.75 [24]. Montazeri et al. reported the Cronbach alpha value associated with the postnatal period as 0.77, with the intra-class correlation coefficient of 0.80 [25].

##### Birth plan checklist

The idea of the birth plan was put forward by Kitzinger in the US in the 1980s [29]. The birth plan was rapidly executed in some European countries and is used in 78% of delivery rooms in England. This includes women’s preferences in labor, mobility, monitoring, pain relief, pharmacological options, acceleration of labor, pushing, respiration and care of the child, and cesarean. It is completed during pregnancy in consultation with healthcare staff or obstetricians by pregnant women [4].

##### PTSD symptom scale 1 (PSS-I)

It includes 17 items that completely cover all criteria of the fourth version of the diagnostic and statistical manual of psychiatric disorders (DSM-IV) to diagnose post-traumatic stress disorder and marks the severity of symptoms of every criterion using a Likert scale. The indicators of this disorder include symptoms associated with re-experiencing (four items), symptoms related to avoidance (seven items), and symptoms pertain to arousal (6 items). In the case of having one or more symptoms of re-experiencing and three or more symptoms related to avoidance, and two or more factors related to arousal, PTSD diagnosis is made. The range of scores is 0–51. The Cronbach alpha of the Persian version of the tool is 0.88, and the Kappa coefficient calculated three test-retest methods has been reported as 1. This questionnaire is completed 4–6 weeks postpartum [30].

##### Partogram form

Partogram is a simple, inexpensive, and valid diagram, which is indeed the best instrument for monitoring the process of delivery as well as maternal and neonatal health. It allows healthcare staff to visually express the details of delivery. It involves registering information regarding the maternal health status, fetal health status, recording the process of delivery, and managing the delivery. Indeed, it is an early warning system that remarkably helps in decision-making on the timely referral of the mother [31].

The reliability and validity of the CEQ 2.0 and EPDS have already been determined and confirmed in the research setting of this plan (Tabriz city). To determine the validity of the birth plan checklist, we will use the translation, content, and face validity of the questionnaire. Specifically, the questionnaires will be filled by ten specialists, the head of the Taleghani Hospital, and 20 mothers. After collecting their opinions, the necessary corrections will be made to the checklist based on the feedback acquired. Also, the reliability of the other questionnaires, including DFS and PSS-I, will be determined through the test-retest method on 20 participants with a two-week interval as well as through specifying the Cronbach alpha coefficient and intra-class correlation coefficient (ICC).

### Data analysis

The obtained information at this phase will be analyzed by SPSS 22. To describe the socio-demographic and obstetrics characteristics, descriptive statistics, including frequency (percentage), mean (SD), in case of normality, will be used, while the median (percentile 25 to 75) will be applied for abnormal data. To compare the variables of the childbirth experience, postnatal depression, post-traumatic symptoms, as well as maternal and neonatal outcomes across the studied groups, in bivariate analysis, one-way analysis of variance and chi-square tests will be used; in multivariate analysis, multivariate linear regression or multivariate logistic regression will be employed by controlling the socio-demographic, obstetrics and delivery characteristics.

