**Methods/design:**

The present study uses a mixed-method with a parallel convergence approach, including both quantitative and qualitative phases. The quantitative phase is a randomized controlled clinical trial performed on 106 pregnant women, 32–36 weeks of pregnancy, referring to Taleghani educational hospital in Tabriz city. The participants will be assigned into intervention and control groups using a randomized block method. A training session will be held about the items of the birth plan checklist at weeks 32–36 of gestation for the participants in the intervention group, whereby a mother-requested birth plan will be developed. It will then be implemented by the researcher after admitting them to the delivery ward. Also, those in the control group will receive routine care. During and after the delivery, the questionnaire of delivery information, neonatal information, and Delivery Fear Scale (DFS) will be completed. Also, a partogram will be completed for all participants by the researcher. The participants in both groups will be followed up until six weeks post-delivery, whereby the instruments of Childbirth Experience Questionnaire (CEQ2.0), Edinburgh’s Postpartum Depression Scale and PTSD Symptom Scale 1 (PSS-I) will be completed six weeks 4–6 weeks postpartum by the researcher through an interview with participants in Taleghani educational hospital. The general linear model and multivariate logistic regression model will be used while controlling the possible confounding variables.

The qualitative phase will be performed to explore the women’s perception of the effect of the birth plan on childbirth experience within 4–6 weeks postpartum. The sampling will be of a purposeful type on the women who would receive the birth plan and will continue until data saturation. In-depth, semi-structured individual interviews would be used for data collection. The data analysis will be done through content analysis with a conventional approach. The results of the quantitative and qualitative phases will be analyzed separately, and then combined in the interpretation stage.

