### The secondary objectives of the quantitative phase are

Comparing the mean duration of the second stage of delivery in the studied groups (having a birth plan, not having a birth plan)Comparing the mean duration of the third stage of delivery in the studied groups (having a birth plan, not having a birth plan)Comparing the mean score of fear of delivery in the studied groups (having a birth plan, not having a birth plan) by controlling the baseline scoreComparing the frequency of vaginal delivery in the studied groups (having a birth plan, not having a birth plan)Comparing the mean PTSD score in the studied groups (having a birth plan, not having a birth plan)Comparing the frequency of neonatal hospitalization in NICU in the studied groups (having a birth plan, not having a birth plan)Comparing the mean postpartum depression score in the studied groups (having a birth plan, not having a birth plan) by controlling the preintervention depression scoreComparing the mean neonatal Apgar score in the first and fifth minutes in the studied groups (having a birth plan, not having a birth plan)

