#### Sample size

The sample size in this study was calculated based on the two variables of “childbirth experience” and “duration of the active phase of labor” using G-power software. Based on the results of the study by Ghanbari Homaei et al. [21] on the variables of childbirth experience and considering m_1_ = 2.71, m_2_ = 3.25 (assuming 20% increase in response to the intervention), sd_1_ = sd_2_ = 0.73, one-sided α = 0.05, and power = 90%, the sample size was calculated 32 participants; considering 10% attrition, the sample size will be 35 in each group. According to the variable of the duration of the active phase of labor and concerning m_1_ = 276.7, m_2_ = 221.4 (assuming 20% reduction in response to intervention), sd_1_ = sd_2_ = 91.3, α = 0.05, and power = 90%, it was calculated as 48 participants, and eventually, it will be 53 as the sample size in each group, given 10% possible attrition. Since the sample size calculated based on the variable of the duration of the active phase of labor would be more extensive. Thus the final sample size was considered 53 in each group.

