##### Socio-demographic and obstetric characteristics questionnaires

This questionnaire will contain items about age, level of education, occupation, having companion, religion, ethnicity, marital status, residence status, household income, being rural or urban, etc. The obstetric questionnaire has items about the number of pregnancies, number of deliveries, number of abortions, history of infertility, etc.

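### The covariate classes named for the logistic models are too many for the binary secondary outcomes in 96 to 106 women, and one class arises after randomisation

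*Protocol article*

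**What the plan says.** The Data analysis section of the quantitative study plans analysis of variance and chi-square tests for the unadjusted comparisons. For the adjusted ones it says that "multivariate linear regression or multivariate logistic regression will be employed by controlling the socio-demographic, obstetrics and delivery characteristics". It gives no covariate list, upper limit or selection rule.

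The section on the socio-demographic and obstetric questionnaires shows what the first two classes contain. Ten socio-demographic items are named: "age, level of education, occupation, having companion, religion, ethnicity, marital status, residence status, household income, being rural or urban". Four obstetric items follow (counts of pregnancies, deliveries and abortions, and infertility history). Both lists are left open-ended. Delivery characteristics come on top and are not itemised.

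The secondary objectives include two binary outcomes. One is "Comparing the frequency of neonatal hospitalization in NICU in the studied groups"; the other is the frequency of vaginal delivery. No expected rate is given for either. The abstract describes the adjustment more loosely, as control of possible confounders.

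**The concern.** A logistic model's capacity depends on the smaller of the numbers of events and non-events, not on the number of women. The trial is sized only on two continuous outcomes, and the exclusion criteria remove high-risk pregnancies, so NICU admission may well be uncommon. A model carrying three whole covariate classes could then give a treatment odds ratio that is exaggerated and imprecise, or have no finite maximum-likelihood solution.

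A second problem is independent of sample size. Delivery characteristics are recorded during or after birth, weeks after allocation at 32 to 36 weeks of gestation. The birth plan is meant to change the course of labour. Adjusting mode of birth or NICU admission for what happened in labour can therefore remove part of the effect the trial sets out to measure.

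**Working it through.** **Number of women.** The abstract says "The quantitative phase is a randomized controlled clinical trial performed on 106 pregnant women". The Sample size section says of the active-phase outcome that "it was calculated as 48 participants, and eventually, it will be 53 as the sample size in each group", "given 10% possible attrition". Its inputs are a difference of 276.7 − 221.4 = 55.3, SD 91.3, α = 0.05 and 90% power. The article calls α one-sided only for childbirth experience.

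- Normal approximation, one-sided: n = 2 × (1.645 + 1.282)² × (91.3 / 55.3)² ≈ 46.7, so 47 per arm. The noncentral t calculation gives 48, as stated. Two-sided it would be 58 or 59, so the stated figure is one-sided.
- Attrition: 48 × 1.1 = 52.8, so 53 per arm.
- Women available: 2 × 48 = 96 after attrition, 2 × 53 = 106 randomised. Both binary outcomes are recorded around delivery, so the true figure may be nearer 106.

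**Number of parameters.** 10 + 4 named items + arm = 15, counting each item once. Items with several categories, the open ends of both lists and the delivery characteristics would add more.

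**Events per parameter** = N × rate / 15. The rates are assumptions.

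| Assumed overall rate | Events, N = 96 | Per parameter | Events, N = 106 | Per parameter |
|---|---|---|---|---|
| 5% | 4.8 | 0.3 | 5.3 | 0.4 |
| 10% | 9.6 | 0.6 | 10.6 | 0.7 |
| 20% | 19.2 | 1.3 | 21.2 | 1.4 |
| 30% | 28.8 | 1.9 | 31.8 | 2.1 |
| 50% (maximum) | 48 | 3.2 | 53 | 3.5 |

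Some items can hardly contribute. Residence in Tabriz city is an inclusion criterion, so rural or urban residence barely varies, and with only first or second deliveries admitted the three obstetric counts are close to redundant. Even with 10 parameters the maximum is only 48 / 10 = 4.8 to 53 / 10 = 5.3.

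**Behaviour of the model.** Simulation with N = 96 and 14 covariates unrelated to the outcome:

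- *No finite fit (any coefficient), 4 continuous and 10 binary covariates with prevalence 10% to 50%:* about 94%, 66% and 23% of datasets at rates of 5%, 10% and 20%.
- *No finite fit, 14 continuous covariates:* about 55%, 8% and 0%.
- *Treatment coefficient itself not finite, mixed covariates:* 52%, 7% and 0%.
- *SD of the treatment log odds ratio, mixed covariates, adjusted against unadjusted:* 0.75 against 0.52 at 20% (0.75 / 0.52 = 1.44) and 0.61 against 0.46 at 30% (1.33). Across runs the increase was about 25% to 50%.
- *True odds ratio 0.5 (log −0.69), mixed covariates:* median adjusted log odds ratio −0.92 at a 20% control rate, an odds ratio of 0.40, and −0.82 at 30%, or 0.44. Across runs the median was about 0.37 to 0.44.

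**Chi-square.** The expected event count per arm is N × rate / 2. It falls below 5 when the overall rate is below 10 / 96 = 10.4%, or 10 / 106 = 9.4%.

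**The case against.** The strongest objection is that the article names classes of covariate and never says that all items enter the model. The abstract's wording fits a short list, and the questionnaire section describes what is collected, not what is modelled. A condensed article may also leave the covariate list and a sparse-data fallback to a fuller document. This stands as far as it goes: that every collected variable will be fitted is an inference a reader might draw, and the absence of a named exact test is not an error. It does not remove the point. The operative analysis text commits to three whole classes, and one of them is post-randomisation however short the final list is.

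Three further readings are tempting but unsupported:

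- *Both binary outcomes will be sparse.* No rate is stated. A low one is plausible for NICU admission but is not shown for mode of birth.
- *The model will usually fail.* At an assumed 10% rate the share without a finite fit runs from about 8% to 66% depending on covariate type. At 10% or above, most failures are a nuisance coefficient diverging while the treatment coefficient stays finite.
- *The chi-square test is invalid.* That holds only if the overall rate is below about 10%.

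Finally, both outcomes are secondary, and the unadjusted comparison is planned in any case.

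**Conclusion.** The point holds in a limited form. Followed as written, the adjustment set is too large for the binary secondary outcomes whatever the event rate, because 15 parameters leave at most 3.2 to 3.5 events each. Where the model mostly fits, at assumed rates of 20% to 30%, the treatment odds ratio is still exaggerated and less precise. At assumed rates of 5% to 10% a finite fit is often lacking, to an extent that depends strongly on the covariates. The simulated figures rest on assumed event rates, on 14 non-prognostic covariates and on assumed covariate types, none of which the article supplies. Adjustment for delivery characteristics is a fault that needs none of these assumptions. The two continuous outcomes on which the trial is sized are outside this calculation, so this is a worthwhile correction, not a threat to the main result.

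**What to change.** For NICU admission and vaginal delivery, make the main analysis the risk difference by allocated arm with a score (Newcombe) 95% confidence interval. Use Fisher's exact test in place of chi-square when an expected cell count is below 5. Limit any adjusted logistic model to arm plus one or two baseline covariates named in advance, such as parity (first or second delivery), and use Firth penalisation when events are sparse. Remove delivery characteristics from the covariates.

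This changes analysis wording only; recruitment, data collection and sample size are untouched. Fully adjusted odds ratios would no longer be reported, and Firth penalisation may need software beyond the named SPSS 22.

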The childbirth experience is an important psychological phenomenon postdelivery whose psychological effects lead to various short-term and long-term adverse health outcomes, with the negative experiences of childbirth being well associated with Post Traumatic Stress Disorder (PTSD) and depression [9–12]. The childbirth experienced is stated to be considered a harmful event for some women [13]. PTSD postdelivery is related to the psychological torments of labor. Generally, 5–20% of women may report delivery-associated traumatic events [14]. According to a systematic review, this prevalence of Post-traumatic stress disorder has been reported to be 25% among Iranian women [15]. Research has shown that the childbirth experience may be affected by a wide range of provisions, including support, external control, internal locus of control, as well as obstetrical complications [13–16].

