### The specific objectives of the quantitative phase are

Comparing the mean score of childbirth experience in the studied groups (having a birth plan, not having a birth plan)Comparing the mean duration of the active phase of delivery in the studied groups (having a birth plan, not having a birth plan)

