#### Sampling

To collect the quantitative data, the researcher would refer to the obstetrics clinic of the Taleghani hospital and would choose the eligible women referring to this clinic through a convenient sampling method. Then, a comprehensive description of the study will be given to the women about the research, its goals, and its methodology, and if they were willing to participate, a written informed consent form would be signed. Next, questionnaires would be completed about the socio-demographic and obstetrical history followed by filling up the Edinburgh’s Postpartum Depression Scale (EPDS) via interview. Note that pregnant women with a depression score of less than 13 will be included.

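### Pre-allocation EPDS is available for every woman but is not named as a covariate for childbirth experience or PTSD symptoms: a small, nearly free gain in precision

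*Protocol article*

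**What the plan says.** **Baseline EPDS exists for everyone.** The EPDS section of the protocol article says "This questionnaire will be completed through an interview by the researcher when the mother refers to routine checkups during 32–36 weeks of gestation". The Sampling section makes it an entry screen: "Note that pregnant women with a depression score of less than 13 will be included". A woman cannot be allocated without a score, and included scores run from 0 to 12.

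**Where it is named as a covariate.** In the list of secondary objectives, the postpartum depression comparison is to control for the score taken before the intervention, and the fear comparison is to control for its own baseline. The PTSD objective has no such addition: "Comparing the mean PTSD score in the studied groups (having a birth plan, not having a birth plan)". Nor does the first specific objective: "Comparing the mean score of childbirth experience in the studied groups (having a birth plan, not having a birth plan)".

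**What the analysis text adds.** The Data analysis section covers childbirth experience, postnatal depression, post-traumatic symptoms and the maternal and neonatal outcomes in one sentence, and says that "multivariate linear regression or multivariate logistic regression will be employed by controlling the socio-demographic, obstetrics and delivery characteristics". EPDS belongs to none of these classes by the article's own layout: it is listed as a separate instrument, and the description of the socio-demographic and obstetric questionnaires does not contain it. The abstract is less specific: "The general linear model and multivariate logistic regression model will be used while controlling the possible confounding variables".

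**The concern.** CEQ 2.0 and PSS-I cannot be measured before the birth, so neither comparison can be adjusted for its own baseline. The usual substitute is a related score taken before allocation. The Background treats the three constructs as connected, with "negative experiences of childbirth being well associated with Post Traumatic Stress Disorder (PTSD) and depression", and the trial restricts entry on antenatal mood. A score of that kind is held for every woman, yet it is named for one outcome only.

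If antenatal EPDS predicts either outcome, two things are lost by leaving it out. Residual variance is larger than it need be, so confidence intervals are wider. A chance difference between the arms in antenatal mood also carries over into the estimated effect. The covariate is best fixed in advance, because choosing covariates after seeing the data invites selective adjustment.

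**Working it through.** **Inputs from the Sample size section.** CEQ means 2.71 and 3.25 (difference 0.54), SD 0.73, one-sided α 0.05, power 90%. Active phase means 276.7 and 221.4 (difference 55.3), SD 91.3, α 0.05, power 90%. Attrition 10%; final size 53 per group.

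**Assumed input.** r, the partial correlation of baseline EPDS with the outcome given the other covariates. The documents give no value. I use 0.1 to 0.4.

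**1. The plan's own figures.** With n = 2(z₀.₉₅ + z₀.₉₀)²(SD/difference)²:
- CEQ: 2 × (1.645 + 1.282)² × (0.73/0.54)² = 31.3, so 32, as stated (33 by the noncentral t).
- Active phase: 2 × (1.645 + 1.282)² × (91.3/55.3)² = 46.7, so 47 (48 by the noncentral t, as stated). This figure reproduces only with a one-sided α.
- Attrition: 32 × 1.1 = 35.2 and 48 × 1.1 = 52.8, matching 35 and 53.

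I therefore take 48 completers per arm.

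**2. CEQ without EPDS.** SE = 0.73 × √(2/48) = 0.149. The 95% half-width is 1.96 × 0.149 = 0.292. Power for 0.54 (noncentral t) is 97.5% one-sided and 94.8% two-sided.

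**3. CEQ with EPDS.** Residual SD = 0.73 × √(1 − r²); effective n per arm = 48/(1 − r²).

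| Assumed r | Variance reduction | Effective n per arm | 95% half-width | Two-sided power for 0.54 |
|---|---|---|---|---|
| 0 | 0% | 48 | 0.292 | 94.8% |
| 0.1 | 1% | 48.5 | 0.291 | 95.0% |
| 0.2 | 4% | 50.0 | 0.286 | 95.5% |
| 0.3 | 9% | 52.7 | 0.279 | 96.4% |
| 0.4 | 16% | 57.1 | 0.268 | 97.5% |

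The degree of freedom spent on the covariate (94 to 93) does not change these figures at the precision shown.

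**4. PSS-I.** The article gives no planned effect or SD. For illustration, a comparison with 80% two-sided power without the covariate has power Φ((1.960 + 0.842)/√(1 − r²) − 1.960) with it: 80.4%, 81.6%, 83.6% and 86.4% at r = 0.1, 0.2, 0.3 and 0.4.

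**5. Chance imbalance.** The standardised baseline difference between arms has SE √(2/48) = 0.204, so its 95% limit is 1.96 × 0.204 = 0.40 SD. An imbalance of that size would shift the unadjusted CEQ difference by 0.40 × r × 0.73. At r = 0.1 this is 0.03 points (5% of 0.54); at r = 0.4 it is 0.12 points (22% of 0.54).

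**6. Is the covariate list closed?** The Data analysis sentence covers postnatal depression but does not name baseline EPDS, although the secondary objectives require it there. It names no baseline fear score either, which the objectives also require. So the list cannot be read as complete, and the two sections need aligning whatever is decided for CEQ 2.0 and PSS-I.

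**The case against.** **Silence is not exclusion.** This stands. The Data analysis list omits scores that the objectives require, and the abstract leaves room for unspecified confounders. A reader might infer that EPDS is deliberately kept out of the CEQ 2.0 and PSS-I models; the article shows only that it is not named there.

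**An article leaves covariate lists to the full protocol or analysis plan.** This stands in part. A missing list would be no finding. Here, however, the article does name covariate classes and assigns baseline scores outcome by outcome, and those two statements do not match.

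**EPDS is not the only antenatal psychological score.** This stands. W-DEQ Version A is planned during pregnancy and concerns childbirth itself. But the Sampling section does not list it among the questionnaires completed at recruitment, so EPDS is the only such score clearly documented as taken before allocation in every woman.

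**The Background does not show that antenatal mood is prognostic.** This stands. It links the experience of birth with later PTSD and depression, and antenatal mood is not among the influences on that experience that it lists. That EPDS predicts CEQ 2.0 or PSS-I is a reasonable assumption, not a documented fact.

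**The gain is flattered by comparison with an unadjusted test.** This largely stands. Other covariates are already planned and entry is cut at 12, and both tend to lower the partial correlation. The low end of the range is the more likely.

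**A reader might infer bias or lost power.** The documents support neither. Randomisation makes the comparison unbiased without EPDS, chance imbalance is already allowed for in the test's error rate, and CEQ has about 95% two-sided power at the planned effect.

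**Conclusion.** The point holds as a minor one. Baseline EPDS is held for every woman, is named as a covariate for postpartum depression only, and is absent from the covariate classes named for two outcomes that have no baseline of their own.

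The cost of leaving it out is some precision and some exposure to chance imbalance. Its size rests wholly on an assumed partial correlation: near 0.1 the gain is negligible (1% of variance), and at 0.4 it is 16%. For CEQ the planned comparison is adequately powered throughout that range. PSS-I was not sized, so any gain there may matter somewhat more, but the article gives no figures from which to measure it. The mismatch between the Data analysis section and the secondary objectives on baseline adjustment does not depend on any assumption.

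**What to change.** In the Data analysis section, state that the linear models for CEQ 2.0 and PSS-I include the pre-allocation EPDS score as a continuous covariate. In the same place, state the two adjustments the secondary objectives already require: baseline EPDS for postpartum depression and the baseline fear score for fear of delivery. If W-DEQ Version A is also completed before allocation in every woman, say so; it could then be considered as a further prespecified covariate.

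The cost is a sentence or two and one degree of freedom per model. No new data are needed, and the sample size does not change.

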### Quantitative study

#### Study design

The quantitative phase of the study is a parallel randomized controlled clinical trial. The target population is pregnant women with a gestational age of 32–36 weeks referring to the obstetrics clinic of Taleghani educational hospital, Tabriz, Iran.

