#### Randomization and allocation concealment

To allocate the participants to the studied groups, a randomized block method with 4- and 6-blocks will be used with an allocation ratio of 1:1. For allocation concealment, the type of intervention is written in a piece of paper and will be placed inside consecutively numbered opaque envelopes. Random allocation and allocation concealment will be conducted by a person not involving in the sampling and data collection. After the study participants signed the consent form, the relevant envelope will be opened, and the intervention will be implemented.

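### The adjusted models control for characteristics of the delivery, which arise after randomisation, so their coefficients would not estimate the total effect of the birth plan

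*Protocol article*

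**What the plan says.** All references are to the protocol article.

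- **Outcomes modelled.** The quantitative Data analysis section sets out its methods "To compare the variables of the childbirth experience, postnatal depression, post-traumatic symptoms, as well as maternal and neonatal outcomes across the studied groups". Bivariate comparisons (one-way analysis of variance, chi-square) come first. In multivariable analysis, linear or logistic regression is then planned "by controlling the socio-demographic, obstetrics and delivery characteristics".
- **Reason for adjusting.** The abstract, under Methods/design, states: "The general linear model and multivariate logistic regression model will be used while controlling the possible confounding variables". It does not mention the unadjusted comparisons.
- **Timing of allocation.** Under Study design of the quantitative study, "The target population is pregnant women with a gestational age of 32–36 weeks". Under Randomization and allocation concealment: "After the study participants signed the consent form, the relevant envelope will be opened, and the intervention will be implemented".
- **Timing of delivery data.** Under Intervention and follow-up, the plan is put into effect when the woman enters the labor ward, and the delivery questionnaire is completed during and after delivery.
- **What a birth plan covers.** The Birth plan checklist section lists preferences on "mobility, monitoring, pain relief, pharmacological options, acceleration of labor, pushing", among others, and ends the list with cesarean.
- **Overlap with outcomes.** Active-phase duration is one of the two specific objectives. Durations of the second and third stages and frequency of vaginal delivery are secondary objectives.
- **Baseline control already planned.** The secondary objectives compare fear controlling for its baseline score, and postpartum depression controlling for the pre-intervention score.

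**The concern.** In a randomised comparison, allocation has no common cause with the outcome except chance. A variable that comes into being after allocation, and that the intervention is designed to change, cannot confound the comparison. It can lie on the path from birth plan to outcome. Conditioning on it takes out the part of the effect that runs through the course of labor. It can also link allocation to unmeasured causes shared by the course of labor and the outcome, which is collider bias.

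The stated aim is to assess the effectiveness of the birth plan, which is a question about its total effect. A coefficient adjusted for how the delivery went answers a different question. Childbirth experience, one of the two outcomes used to size the trial, is among the outcomes modelled this way.

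**Working it through.** **1. Are delivery characteristics post-randomisation?** The Data analysis section names obstetric and delivery characteristics as separate groups. The section on the socio-demographic and obstetric questionnaires places past deliveries, with numbers of pregnancies and abortions, under obstetric history. The delivery group is therefore most naturally the index delivery. Those data are collected weeks after allocation and after the birth plan has been put into effect.

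**2. Are they on the causal path by the article's own account?** The Background expects the birth plan to promote physiological delivery, improve control of labor and lower the cesarean rate. It also says that obstetrical complications may affect the childbirth experience, and it ties negative experience to PTSD and depression. Both links, plan to delivery and delivery to outcome, are thus proposed in the article.

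**3. Design values (Sample size section).**
- Childbirth experience: means 2.71 and 3.25, SD 0.73. Planned effect 3.25 − 2.71 = 0.54.
- Active-phase duration: means 276.7 and 221.4, SD 91.3. Planned effect 221.4 − 276.7 = −55.3 (the section states no unit).

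The article's sample sizes were reproduced first, to confirm that these values were read correctly. With one-sided α = 0.05 and 90% power:
- Experience: the normal approximation gives 32 and the t calculation 33; the article states 32.
- Duration: the normal approximation gives 47 and the t calculation 48; the article states 48.
- Attrition: 48 × 1.1 = 52.8, rounded up to the stated 53.

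**4. Effect of adjusting for one delivery variable.** For a linear model with allocation and a post-randomisation variable M:

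adjusted effect = total effect − b × (arm difference in M), with b = r × SD_Y / SD_M

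Here r is the within-arm correlation of M with the outcome. The article gives no value, so r is assumed. With M = active-phase duration, the part removed is r × (0.73 / 91.3) × (−55.3):

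| Assumed r | Removed | Share of 0.54 | Expected adjusted effect |
|---|---|---|---|
| −0.2 | 0.088 | 16% | 0.45 |
| −0.3 | 0.133 | 25% | 0.41 |
| −0.4 | 0.177 | 33% | 0.36 |

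A simulation with 48 per arm and a true total effect of 0.54 returned 0.54 unadjusted and 0.41 adjusted at r = −0.3, in agreement with the formula.

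**5. What the formula shows about direction.** The change is zero if the arms do not differ in M or if r = 0. With a positive r the coefficient would rise above 0.54 instead of falling. The table therefore shows a possible size under stated assumptions. It does not predict a direction.

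**The case against.** The strongest reply is that unbiased comparisons are already in the plan. The analysis of variance and chi-square tests in the same sentence do not depend on any covariate, and no section ranks the adjusted models above them. This stands, and it confines the point to the adjusted results. It does not remove it. The abstract names only the adjusted models, and if the two sets disagree the article does not say which one answers the question.

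Second, the delivery items are never listed, and the article condenses a fuller plan. That also stands. The exact covariates are unknown, but the adjustment set itself is stated positively, and a reading in which the delivery group predates randomisation is implausible.

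Third, the Birth plan checklist section describes birth plans in general, and the trial's own checklist was still to be validated. This is a fair caution about particular items. The Background still states what the intervention is expected to change.

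Fourth, baseline control of fear and depression is already planned under the secondary objectives. That is correct and is credited here. Fear is also not named in the Data analysis sentence, and falls under it only if counted as a maternal outcome.

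Three stronger readings are tempting, and the document does not support them:
- A reader might infer that an outcome such as mode of birth would be adjusted for itself. The article does not say that every delivery variable enters every model.
- A reader might infer that adding further delivery variables must remove more of the effect. With shared causes in play, the direction is unknown.
- A reader might infer that a true benefit would go unseen. The unadjusted estimates are still planned.

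**Conclusion.** The point holds for the adjusted models only. As worded, the adjustment set includes variables that most naturally arise after randomisation, that the birth plan is meant to influence, and that overlap with the trial's own outcomes. Coefficients from these models would not estimate the total effect of the birth plan and may carry collider bias of unknown direction.

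The size cannot be derived from the document. The 0.09 to 0.18 loss (16–33% of 0.54) rests on three assumptions: the full planned reduction of 55.3 in active-phase duration occurs, the within-arm correlation with the experience score is −0.2 to −0.4, and duration is the only delivery variable in the model.

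Nothing here requires an adjusted model to be primary. An unadjusted primary comparison with supporting adjusted models would be equally sound, and that choice is the sponsor's.

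**What to change.** In the quantitative Data analysis section, delete delivery characteristics from the adjustment set and restrict adjustment to variables measured before randomisation. Examples are parity from the obstetric history, and the baseline depression and fear scores that the secondary objectives already name. Bring the abstract's phrase on confounding variables into line.

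Report characteristics of the delivery as outcomes. If a model containing them is wanted, label it as an exploratory mediation analysis and do not present it as the effect of the birth plan.

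The cost is about one sentence in the analysis section and a matching edit in the abstract. No new data are needed, and the sample size stays at 53 per group.
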